### **3.2 Recruitment, screening and informed consent procedure** (specific schedule of assessments for each patient is summarized in appendix 1)

Patient follow-up will be performed according to local guidelines, without introducing any modification due to the participation in the study. Besides current standard of care, clinical, ultrasonographic biochemical and biophysical parameters will be collected. Women will have the possibility to deny their participation or to withdraw from the study at any point. Likewise, their participation (or their denial) will not imply any change in the medical management of the pregnancy.

The recruitment, the standard of care and the data collection organization will be as follows:

- (1) The pregnant woman will have her ordinary medical appointment at 34-38 weeks of gestation.
- (2) Once finished the conventional medical consultation, eligibility criteria will be reviewed. If eligible, they will be offered to be enrolled in the study. After giving all the required information (which will include a specific information sheet), if the woman accedes to participate, informed consent form will be signed. Women will be encouraged to consider their decision and to ask all questions between this appointment and the following.

### **3.3 Study procedures**

- (1) If the woman consents her participation, she will be scheduled at 385/7-396/7 weeks of pregnancy for assessment.
- (2) During the visit, one of the researchers will perform:
  - a. Review of clinical records and directed interview with the pregnant women in order to collect the required variables.
  - b. Woman will be asked to empty her bladder
  - c. Vaginal sample will be obtained using a sterile speculum and quantitative determination of fetal fibronectin and the qualitative determination of Placental Alpha Microglobulin-1 will be performed *in situ*, with the available commercialized kits for this purpose. The results of the tests will be registered, and the vaginal samples and the single-use medical devices will be discarded following hospital guidelines. We will also measure cervical stiffness using Pregnotia system device at this time. The Pregnotia System measurements are done according to the Instruction for use. The study team will be trained to ensure the right handling of the device. During the speculum application 3 consecutive cervical stiffness measurements at 12 o'clock position will be obtained (CSI 1, CSI 2, CSI 3) and reported in the CRF. Cervical stiffness measurement is only valid if the first measurement was successful.
  - d. Transvaginal ultrasonographic scan will be performed and images will be recorded for off-line analysis.
  - e. Transabdominal ultrasonographic scan will be performed to assess estimated fetal weight. The result will be blinded to the patient and it will only be registered in the case report form (to blind the result from the attending physicians).
- (3) If any anomaly is detected during the ultrasound scan, the women will be referred and managed according to current guidelines.
- (4) All results will be blinded to physicians in charge and to the participants (double blind). All extracted data will be recorded, and the researcher will ask the woman if she is willing to continue with her participation. If so, a further appointment will be scheduled at 40 weeks of pregnancy (minimum 1

week after the last visit), if labor does not start. Follow-up of the pregnancy will be performed in accordance to current standard of care, with her attending obstetrician or midwife.

- a. From the 429 recruited participants, we expect that 60% will remain undelivered for the next consultation (257 women).
  - b. This means that, for all women, an initial set of data will be collected. However, more than half of them will have a second determination.
  - c. Therefore, for 429 women, 686 evaluations will be performed.
- (5) Women initially approached at 40 weeks of pregnancy will be also eligible, as they will be included in the secondary stratified analysis.
  - (6) If labor does not spontaneously start during follow-up, in the absence of maternal or fetal conditions requiring early delivery, women will be scheduled for induction of labor between 41 and 42 weeks of pregnancy, following local guidelines.
  - (7) Clinical data, specific variables and perinatal outcomes will be recorded in an electronic case report form specifically designed for this purpose, adequately codified and anonymized, in order to avoid the possibility of identification and association of sensible data to concrete participants. All the information will be confidentially handled and will remain digitalized in an informatized database, password protected and only accessible by the main researcher. Data will be encoded for any kind of transport and all forms will be destroyed following current legislation.

[figure not shown]

## Study plan

|                                                  | 2019 |    |   |    |     | 2020 |    |     |    |   |    |     |      |    |   |    |     |
|--------------------------------------------------|------|----|---|----|-----|------|----|-----|----|---|----|-----|------|----|---|----|-----|
|                                                  | VIII | IX | X | XI | XII | I    | II | III | IV | V | VI | VII | VIII | IX | X | XI | XII |
| Database creation                                |      |    |   |    |     |      |    |     |    |   |    |     |      |    |   |    |     |
| Elaboration of data collection form              |      |    |   |    |     |      |    |     |    |   |    |     |      |    |   |    |     |
| Recruitment                                      |      |    |   |    |     |      |    |     |    |   |    |     |      |    |   |    |     |
| Review of data, filtering and mistake correction |      |    |   |    |     |      |    |     |    |   |    |     |      |    |   |    |     |
| Multicentric meetings                            |      |    |   |    |     |      |    |     |    |   |    |     |      |    |   |    |     |
| Amendment submission                             |      |    |   |    |     |      |    |     |    |   |    |     |      |    |   |    |     |

|                                                  | 2021 |    |     |    |   |    |     |      |    |   |    |     | 2022 |    |     |    |   |
|--------------------------------------------------|------|----|-----|----|---|----|-----|------|----|---|----|-----|------|----|-----|----|---|
|                                                  | I    | II | III | IV | V | VI | VII | VIII | IX | X | XI | XII | I    | II | III | IV | V |
| Recruitment                                      |      |    |     |    | + |    |     |      |    |   |    |     |      |    |     |    |   |
| Review of data, filtering and mistake correction |      |    |     |    |   |    |     |      |    |   |    |     |      |    |     |    |   |
| Kick-off meetings (online)                       |      |    |     |    |   |    |     |      |    |   |    |     |      |    |     |    |   |
| Monitoring visits                                |      |    |     |    |   |    |     |      |    |   |    |     |      |    |     |    |   |
| Wrap-up meetings (presential)                    |      |    |     |    |   |    |     |      |    |   |    |     |      |    |     |    |   |
| Image analysis                                   |      |    |     |    |   |    |     |      |    |   |    |     |      |    |     |    |   |
| Statistical analysis                             |      |    |     |    |   |    |     |      |    |   |    |     |      |    |     |    |   |
| Conclusions                                      |      |    |     |    |   |    |     |      |    |   |    |     |      |    |     |    |   |
| Communication of results                         |      |    |     |    |   |    |     |      |    |   |    |     |      |    |     |    |   |

+ Start of multicenter collaboration

### POSSIBLE LIMITATIONS

- (1) *Women's refusal to participate*: all the suggested exams are commonly performed during pregnancy (transvaginal scan) or easily grabbed by routine vaginal exploration (fetal Fibronectin and Placental Alpha Microglobulin 1). Besides, as the participation does not imply any change in current standard of care, women are not exposed to subsequent risks due to their enrolment.
- (2) *Bad quality images*: in order to avoid the interprofessional variability, the researcher team will be reduced to the minimum. Also, specific training will be offered in order to homogenize image acquisition criteria.
- (3) *Women excluded due to findings in the ultrasound scans*: As ultrasonographic examination will be performed, there is a risk of finding anomalies in the scans which may prompt medical advice, leading to a possible exclusion of the participant from the study. If this happens, this situation will be recorded. However, to try to compensate this potential situation, sample size has been increased by 20%.

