### SAMPLE SIZE

According to our data, approximately 78% of women will start their labor spontaneously before 41 weeks, meaning that 22% will have an induction of labor for medical reasons other than gestational age. Hence, considering 10 events (spontaneous onset of labor) for each of these 15 variables, and doubling this quantity for the elaboration of two different models, 13 participants will be required for each of these variables, hence 390 women are needed. Assuming a 10% rate of women with missing values in at least one predictor, 429 **patients** are needed.

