### **3.4 Withdrawal and discontinuation**

Women may abandon the study at any time upon request, if they decide to withdraw their informed consent. In this case, they will be asked to decide about the destination of the information that has already been collected.

- If she decides not to consent any use of their data, the corresponding entrance will be removed from the database and all the paper documentation regarding their participation will be destroyed, complying with legal requirements.
- If she decides to consent the utilization of data, it will be kept as the rest of the data and the follow-up will be censored at the time of consent withdrawal.

It may also be possible that women discontinue their participation if a medical indication for elective cesarean delivery or induction of labor (different from gestational age) arises during the follow-up. In this case, censorship will be established at this point.

If perinatal outcomes are missing (due to delivery in another center, for example), follow-up will be considered up to the last medical registry and censored afterwards.

This potential loose of information has been considered in the design and the sample size has been adequately adjusted.

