### 4.2. Handling of missing data

As it has been mentioned in the sample size estimation, the required number of participants has been increased in order to compensate potential loss, mainly due to the arising of medical complications that may lead to elective cesarean deliveries or to an induction of labor due to causes different from gestational age. We consider that delivering outside the Hospital is an unlikely event, as the eligibility criteria specify that women plan to deliver within the center.

Missing data in the predictive variables will lead to the exclusion of the participant from the regression models. Hence, a 10% increase in sample size has been estimated to compensate this issue.

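### The protocol claims a 20% sample-size increase for ultrasound exclusions, but the 429 contains only a 10% increase, and that is assigned to missing predictors

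*Protocol*

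**What the plan says.** The sample size in the protocol, section 3.1, rests on an events-per-variable rule, "considering 10 events (spontaneous onset of labor) for each of these 15 variables, and doubling this quantity for the elaboration of two different models". It takes the event rate from local data: "approximately 78% of women will start their labor spontaneously before 41 weeks". The remaining 22% are described as having induction for medical reasons other than gestational age. From this, "13 participants will be required for each of these variables, hence 390 women are needed". One allowance follows: "Assuming a 10% rate of women with missing values in at least one predictor", which brings the total to 429. Section 3.3 uses 429 as the number recruited.

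Three other places describe what the total covers:

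- Section 3.3, Possible limitations, item (3), on women excluded because of ultrasound findings: "to try to compensate this potential situation, sample size has been increased by 20" per cent.
- Section 3.4, after listing withdrawal of consent, medical indications arising in follow-up and missing perinatal outcomes: "This potential loose of information has been considered in the design and the sample size has been adequately adjusted".
- Section 4.2, which says the number was raised for losses due mainly to medical complications and then, for missing predictors, that "a 10% increase in sample size has been estimated to compensate this issue".

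**The concern.** Sections 3.1 and 3.3 give different inflation figures for one total, 10% and 20%, and only one of them can be found in the arithmetic. The 10% has a declared use, missing predictors. If nothing else was added, the protocol tells its readers that ultrasound exclusions, withdrawals and missing outcomes are provided for when the number holds no allowance for them. Anyone judging whether recruitment of 429 is enough would rely on a margin that does not exist.

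**Working it through.** The check takes the plan's own event definition (spontaneous onset), 78% event rate, 15 variables and two models as given.

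**Reproducing the stated figure (section 3.1)**

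- Events required: 10 x 15 x 2 = 300.
- Women per variable: 10/0.78 = 12.8, rounded up to 13.
- Base number: 13 x 15 x 2 = 390.
- With the 10% increase: 390 x 1.10 = 429, an exact match. Conversely, 429/390 = 1.10.

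**Looking for the 20% (section 3.3, Possible limitations)**

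- 20% increase alone: 390 x 1.20 = 468, which is 39 more than 429.
- 10% and 20% increases together: 390 x 1.10 x 1.20 = 514.8, so 515, which is 86 more than 429.
- The step from 10 to 13 women per variable is not a concealed 20%. It converts events to women at the 78% rate.

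**What 429 yields if 10% of women have a missing predictor**

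- Complete cases: 429 x 0.90 = 386.1, about 386.
- Events: 386.1 x 0.78 = 301.2, about 301.
- Women needed for 300 events without rounding per variable: 300/0.78 = 384.6, so 385.
- Reserve: 386 - 385 = about one woman.

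**Effect of any further loss.** The protocol gives no rate for ultrasound exclusions, withdrawal or missing outcomes. The rates below are assumptions for illustration, applied on top of the 10%.

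| Further loss (assumed) | Women | Events |
|---|---|---|
| 0% | 429 x 0.90 = 386 | 301 |
| 2% | 429 x 0.90 x 0.98 = 378 | 295 |
| 5% | 429 x 0.90 x 0.95 = 367 | 286 |

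**The case against.** The best defence is that the practical consequence is small and that part of the claimed adjustment is real. Much of this stands.

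- **Medical indications are provided for.** Going from 300 to 390 allows for the 22% induced for medical reasons. That is one of the losses named in section 3.4 and the main one named in section 4.2, so it would be wrong to say that the 429 contains nothing except the 10%.
- **Some losses are partial.** Section 3.4 censors women with missing outcomes and those who withdraw but let their data be kept, so they still contribute to the survival model. Section 4.2 calls delivery elsewhere unlikely.
- **The form of the 10% is a minor matter.** A reader might infer that using 390 x 1.10 in place of 390/0.90 = 434 leaves the study too small. The gap is 5 women, and 301 events still meet the 300 required.
- **The 20% is not a loss rate.** A reader might multiply 429 by 0.90 and 0.80 and report 309 analysable women. Section 3.3 states an increase in sample size and speaks of exclusion only as a possibility. It does not forecast that 20% will be lost.
- **Women first seen at 40 weeks.** A reader might think they use up places in the 429. Section 3.3 admits them with the statement that "Women initially approached at 40 weeks of pregnancy will be also eligible, as they will be included in the secondary stratified analysis", and nothing in the protocol counts them toward the 429.
- **Complete-case deletion.** A reader might want it replaced by imputation. That is a debatable choice of method and does not bear on the contradiction between 10% and 20%.

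None of this accounts for the 20%. No route through the stated inputs reaches 429 with that increase included.

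**Conclusion.** The statement in section 3.3 is wrong as written. The total contains a 10% increase, not 20%, and sections 3.1 and 4.2 use that 10% for missing predictors. The claimed increase would require 468 women, or 515 with the 10% as well. The total also includes the conversion for medical inductions, but it has no separate allowance for ultrasound exclusions, withdrawals with data removal or unknown outcomes, so the assurance in section 3.4 is only partly supported.

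The documents do not show that the study is materially undersized. At the assumed 10% of missing predictors the plan's own basis is just met, with about 386 women and 301 events against 385 and 300. What is missing is the reserve: an assumed further loss of 2% would bring the events to about 295, and 5% to about 286. These conclusions depend on the protocol's 78% event rate and its 10% missing-predictor rate.

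**What to change.** - **Section 3.3, Possible limitations, item (3):** remove the claim of a 20% increase.
- **Sections 3.4 and 4.2:** say that the 429 includes two things, the conversion from 10 events to 13 women per variable for the 22% with medical induction, and a 10% increase for missing predictors. Say also that there is no separate allowance for ultrasound exclusions, withdrawal or missing outcomes.
- **Section 3.1:** state the expected analysable number as about 386 women and about 301 events, before any such further loss. The difference between 390 x 1.10 = 429 and 390/0.90 = 434 can be noted in passing.

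The cost is a change of wording and a slightly less favourable stated figure. No additional women are required.

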### **3.4 Withdrawal and discontinuation**

Women may abandon the study at any time upon request, if they decide to withdraw their informed consent. In this case, they will be asked to decide about the destination of the information that has already been collected.

- If she decides not to consent any use of their data, the corresponding entrance will be removed from the database and all the paper documentation regarding their participation will be destroyed, complying with legal requirements.
- If she decides to consent the utilization of data, it will be kept as the rest of the data and the follow-up will be censored at the time of consent withdrawal.

It may also be possible that women discontinue their participation if a medical indication for elective cesarean delivery or induction of labor (different from gestational age) arises during the follow-up. In this case, censorship will be established at this point.

If perinatal outcomes are missing (due to delivery in another center, for example), follow-up will be considered up to the last medical registry and censored afterwards.

This potential loose of information has been considered in the design and the sample size has been adequately adjusted.

## 4 STATISTICS AND METHODOLOGY

### 4.1. Statistical analysis plan

#### MAIN ANALYSIS

The main outcome (spontaneous onset of labor vs. induction of labor between 41 and 42 weeks of pregnancy due to gestational age) will define two groups. The distribution of continuous or categorical variables among the units will be compared using Student's T test or Fischer's exact test, respectively. Two-sided significance level was set to 0.05.

A model of prediction of the binary outcome will be elaborated using stepwise backward and forward logistic regression analysis, including all analyzed features (gestational age at data collection will be included as an independent variable). To add or remove variables from the model, p-values of 0.05 or 0.10 will be used, respectively. Goodness-of-fit of the model will be evaluated using Hosmer and Lemeshow test and, if multiple models are achieved, the best one will be selected searching parsimony and following Akaike's Information Criterion. Area under the Receiver-Operating Characteristics curve will be used to assess predictive ability of the model. This value will be also calculated using bootstrapping resampling methods (1000 repetitions) to internally validate the results. As only a subset of the sample will have the measurement of cervical stiffness using Pregnotia device (as this assessment was lately introduced), a secondary analysis (following the same principles of the main analysis) will be performed. A correlation analysis will be carried out comparing cervical consistency index evaluated by ultrasound with cervical stiffness assessed using the aspiration device, as both measurement evaluate the same biophysical characteristic of the cervix.

The probability of spontaneous onset of labor for each day after the analysis will be evaluated using survival regression models. The data will be described using Kaplan-Meier's non-parametrical survival function and the predictive model will be estimated using stepwise backward and forward Cox's regression (proportional hazards model). As mentioned before, data regarding women whose labors have been induced due to maternal or fetal indication (different from gestational age) or with prelabor rupture of membrane without spontaneous onset of labor after 12 hours of expectant management will be censored at the time of admission for these causes.

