## 2.2 Primary and secondary endpoints

| VARIABLE TYPE                                      |  | VARIABLE AND SOURCE OF INFORMATION                                                                                                                                                                 |                       |
|----------------------------------------------------|--|----------------------------------------------------------------------------------------------------------------------------------------------------------------------------------------------------|-----------------------|
| Main outcome (1)
(logistic regression analysis) |  | Spontaneous onset of labor between 39 and 41 3/7 weeks of pregnancy
vs.
Induction of labor between 41 3/7 and 42 weeks of pregnancy due to gestational age             |                       |
|                                                    |  | Gestational age at spontaneous onset of labor (days after last menstrual period)                                                                                                                   |                       |
| Main outcome (2)
(survival analysis)            |  | Gestational age at spontaneous onset of labor (days after last menstrual period)                                                                                                                   |                       |
| Censorship                                         |  | Induction of labor due to maternal or fetal indication, different from gestational age.
Prelabor rupture of membrane without spontaneous onset of labor after 12 hours of expectant management. |                       |
| Predictors                                         |  |                                                                                                                                                                                                    |                       |
| Clinical                                           |  | Maternal age (years)
Maternal height (cm)
Closest to admission maternal weight (kg)
Previous vaginal deliveries
Previous cesarean deliveries
Expected delivery date                 |                       |

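### The binary main outcome is defined in two incompatible ways (sections 2.2 and 4.1), and the section 2.2 version leaves some uncensored women in neither group

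*Protocol*

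**What the plan says.** Gestational age is written below as weeks+days.

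- **Section 2.2, Main outcome (1), logistic regression.** The event is "Spontaneous onset of labor between 39 and 41 3/7 weeks of pregnancy". The comparator is "Induction of labor between 41 3/7 and 42 weeks of pregnancy due to gestational age".
- **Section 4.1, Main analysis.** The same outcome is given as "spontaneous onset of labor vs. induction of labor between 41 and 42 weeks of pregnancy due to gestational age", and the protocol says that it "will define two groups". The spontaneous group has no date limits, and the comparator starts at 41+0 instead of 41+3.
- **Section 3.3, item (6).** If labor has not begun and nothing requires earlier delivery, "women will be scheduled for induction of labor between 41 and 42 weeks of pregnancy, following local guidelines".
- **Section 3.3, item (1).** After consent, "she will be scheduled at 38 5/7 -39 6/7 weeks of pregnancy for assessment", so follow-up can begin at 38+5.
- **Censoring (sections 2.2, 3.4 and 4.1).** The first cause listed is "Induction of labor due to maternal or fetal indication, different from gestational age". The others are membrane rupture without labor after 12 hours, a newly arising indication for elective cesarean, withdrawal of consent, and missing perinatal outcomes.

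The protocol does not say whether section 2.2 or section 4.1 governs.

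**The concern.** A binary main outcome should place each analysable woman in one of two groups. Here the two statements of that outcome disagree on the lower limit of the comparator and on both limits of the spontaneous group. Who enters the main logistic model, and hence its area under the curve and bootstrap validation, depends on which section the analyst follows. If this stays open, the choice could be made after outcomes are known.

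The section 2.2 version has a second problem. It removes women by the day on which labor began or was induced, which nobody knows at the assessment at about 39 weeks, when the model is meant to be used. Among spontaneous labors it removes the latest ones, plausibly the women most like the comparator. That could make discrimination look better than it is, although the protocol gives no data to confirm it.

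**Working it through.** **Inputs.** The outcome windows come from sections 2.2 and 4.1. The care window of 41 to 42 weeks comes from section 3.3(6), and the earliest assessment at 38+5 from section 3.3(1). The sample-size inputs come from section 3.1: 78% spontaneous onset, 10 events per variable, 15 variables, two models and a 10% allowance.

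**Step 1: the plan's own figure.** 10 / 0.78 = 12.8, rounded up to 13 women per variable. 13 × 15 × 2 = 390, and 390 × 1.10 = 429. The stated 390 and 429 reproduce. Neither outcome window enters this calculation.

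**Step 2: classify each day under both definitions, boundaries inclusive.** Spontaneous onset can fall on any of 24 days from 38+5 to 42+0. Induction for gestational age can fall on any of 8 days from 41+0 to 42+0.

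| How labor began | Day | Section 2.2 | Section 4.1 |
|---|---|---|---|
| Spontaneous | 38+5, 38+6 | neither group | spontaneous |
| Spontaneous | 39+0 to 41+3 | spontaneous | spontaneous |
| Spontaneous | 41+4 to 42+0 | neither group | spontaneous |
| Induced for gestational age | 41+0, 41+1, 41+2 | neither group | induction |
| Induced for gestational age | 41+3 to 42+0 | induction | induction |

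The definitions disagree on 2 + 4 + 3 = 9 of the 24 + 8 = 32 combinations of onset type and day. In all nine, section 2.2 gives no group and section 4.1 gives one. The day 41+3 lies in both section 2.2 windows, but the type of onset still separates the groups.

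**Step 3: does censoring place these women?** No. The induced women were induced for gestational age, and the censoring rule is limited to other indications. The spontaneous women had the event. Withdrawal, lost outcomes and membrane rupture without labor describe other women. Section 4.1 also states its censoring rule for the survival model, and a logistic model has no censoring time.

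**Step 4: how many women?** The protocol gives no share of women induced for gestational age, no distribution of induction days and neither centre's policy. If both centres start such inductions at 41+3, no comparator woman is lost. The total is then zero if no one also labors before 39+0 or from 41+4. For assumed shares of the 390 analysable women:

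- 2%: 390 × 0.02 = 7.8, about 8 women
- 5%: 390 × 0.05 = 19.5, about 20 women
- 10%: 390 × 0.10 = 39 women

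**The case against.** The strongest reply is that the parenthesis in section 4.1 is shorthand for the section 2.2 table and that the 41+3 cut is deliberate. The cut ensures that every non-event was managed expectantly to a common point. Under section 4.1, a woman induced at 41+0 is a non-event although she had no chance to labor at 41+1 to 41+3, while a woman at another centre who labors at 41+2 is an event. Local policy then enters the outcome itself.

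Much of this stands. The protocol does not settle which window was intended, and the section 4.1 definition carries that cost. The shorthand reading does not remove the problem. The limits differ in substance, and if section 2.2 governs, the protocol still needs a rule for the women whom it leaves out.

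A reader might infer four stronger points, which the protocol does not support:

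- **That there are four rival definitions.** Section 3.3(6) describes routine care under local guidelines. The phrase "approximately 78% of women will start their labor spontaneously before 41 weeks" in section 3.1 is a planning assumption. Only sections 2.2 and 4.1 define the outcome.
- **That the comparator shrinks severely.** If 10% of 390 (39 women) were induced for gestational age, and one third to two thirds of them before 41+3, 13 to 26 would remain. Both inputs are assumptions, and the loss may be zero. A centre that induces before 41+3 is possible under section 3.3(6) but is not documented.
- **That the main analysis as a whole fails.** Main outcome (2), gestational age at spontaneous onset, uses none of these windows, so late and very early spontaneous labors remain events there.
- **That the 41+3 cut is wrong and must be deleted.** It may be intended. The error is that two definitions coexist and one is incomplete.

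The 38+5 to 38+6 group is probably small. It requires assessment and labor within the same two days, and women with symptomatic contractions are excluded.

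**Conclusion.** The contradiction is certain from the text and concerns one of the two main outcomes. Following section 2.2 drops three identifiable sets of uncensored women from the logistic model on post-assessment information; following section 4.1 drops none of them. The number of women is unknown: from zero upward, and about 8 to 39 of 390 under assumed shares of 2% to 10%. The direction and size of any effect on discrimination cannot be derived from the protocol. The point should be settled before analysis because it decides who is in the main logistic model.

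**What to change.** Before outcomes are analysed, state one definition of the binary main outcome in both sections 2.2 and 4.1 that assigns every uncensored woman to a group. The simplest choice is the section 4.1 wording: event, any spontaneous onset after assessment; non-event, induction with gestational age as the recorded indication. Keep the section 2.2 windows as a sensitivity analysis, and report how many women they exclude, by reason and centre. If the sponsor prefers the windows as primary, the protocol should say explicitly that these women are excluded and why.

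The wording of the induction window in sections 2.2, 3.3(6) and 4.1 should also be reconciled. No timing of induction is proposed here.

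The cost is a text change and one extra model fit. Applying the censoring rule already requires the reason for induction and the date of admission, but the protocol lists no case report form fields for them, so confirm that both are recorded. The drawback is that women induced at 41+0 to 41+2 count as non-events after less time in which to labor. Comparing the two analyses would show how far the results depend on this.
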